### Provisions for post-trial care {30}

All study participants stay under medical supervision during the study period. Should any severe drug adverse reaction to pregabalin occur, specialist consultations are available. After the trial period, the patients are provided with standard, usual care.

### Outcomes {12}

The primary outcome measure will be total oxycodone consumption 24 h after surgery. Secondary outcome measures will be as follows: pain scores on the NRS scale at 1, 6, 12, and 24 h after surgery, postoperative sedation on the Ramsay scale [25], PONV impact scale [26], the incidence of desaturation episodes < 94% and episodes of blurred vision at 1, 6, 12 and 24 h after surgery, intraoperative heart rate (HR), systolic blood pressure (SBP), diastolic blood pressure (DBP), mean blood pressure (MBP): their highest and lowest values, time of MAP < 65 mmHg, > 90 mmHg, HR < 50 and > 90, total fluid volume, total ephedrine dose and patient's comfort assessed in QoR-40 [22] questionnaire at discharge.

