**Methods:**

The study is designed as a prospective randomized controlled trial with double-blinding. Randomization will be performed in a block with a parallel 1:1 allocation. The intervention will involve receiving a pregabalin 150 mg capsule 1–2 h before the surgery, whereas the control group will receive an identically looking placebo. The primary outcome measure will be total oxycodone consumption in the first 24 h following surgery. Secondary outcome measures will be pain severity assessed using the Numerical Rating Scale (NRS) 1, 6, 12, and 24 h after surgery, postoperative sedation on the Ramsay scale, PONV impact scale, the incidence of desaturation episodes < 94%, and episodes of blurred vision at 1, 6, 12, and 24 h after surgery, intraoperative hemodynamic parameters such as heart rate (HR), systolic blood pressure (SBP), diastolic blood pressure (DBP), mean blood pressure (MBP), total fluid volume, and total ephedrine dose. Patient comfort will be additionally assessed using the QoR-40 questionnaire at discharge.

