### Objectives {7}

Our study aims to assess, in the patients with obesity undergoing LSG, what is the difference in total oxycodone consumption (applied by the PCA pump) between preemptive oral pregabalin 150 mg administration compared with placebo, 24 h after the operation. We hypothesized that the investigated intervention would reduce opioid use and improve recovery with potentially fewer opioid side effects, as well as provide similar intraoperative hemodynamical stability.

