### Participant timeline {13}

The participant timeline is detailed in Table 1.

**Table 1 Tab1:** The participant timeline

	Study period							
	Enrollment	Allocation	Post-allocation					
Timepoint	− 1 day	Day of surgery	Surgery	1 h	6 h	12 h	24 h	Discharge
Enrollment:								
Eligibility screen	X							
Informed consent	X							
Allocation		X						
Interventions: pregabalin or placebo		X						
Assessment:								
Baseline variables	X	X						
Total oxycodone				- >	- >	- >	X	
The NRS scores				X	X	X	X	
Ramsay Score				X	X	X	X	
PONV-Impact score				X	X	X	X	
SatO2 < 94%				X	X	X	X	
Blurred vision				X	X	X	X	
Intraoperative SBP, DBP, MBP and HR			X					
Total fluid			X					
Total ephedrine			X					
QoR-40								X

Enrolment — 1 day before the operation, intervention — 1 to 2 h before surgery, assessments — 24 h postoperatively

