### Plans to promote participant retention and complete follow-up {18b}

Data will be collected during the hospital stay. At the end of the hospital stay, as a standard 24 h after the surgery, study subjects will be encouraged to fill in the QoR-40 questionnaire.

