#### Statistical methods for numerical outcomes with one-time measurement

For numeric outcomes involving a single measurement point (e.g., total oxycodone consumption at 24 h, comparison of lowest and highest BP and HR values, duration of MBP below 65 mmHg or above 90 mmHg, HR below 50/min, and HR above 90/min, total fluid volume administered, total ephedrine usage during surgery, QoR-40 score at discharge), the significance of differences between the study group and the control group will be assessed using the Wilcoxon sum rank test. This non-parametric test is chosen based on the assumption that the distributions of these numerical variables do not conform to a normal distribution. For each outcome variable, the median and interquartile range (IQR) will be reported for both the study and control groups. In addition to the *p*-values, the Wilcoxon effect size (*r*) will be calculated to quantify the magnitude of the difference between the groups. Where possible, 95% confidence intervals for median differences between groups will be reported to provide an estimate of the precision of the observed effects.

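### QoR-40 is tied to discharge, which is 24 h only as a standard, so the comparison may be biased if length of stay differs between arms

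*Protocol article*

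**What the plan says.** All references are to the Protocol article.

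- **Abstract, Methods:** "Patient comfort will be additionally assessed using the QoR-40 questionnaire at discharge".
- **Outcomes {12}:** the last secondary outcome is patient "comfort assessed in QoR-40 [22] questionnaire at discharge". Pain, sedation, PONV impact, desaturation and blurred vision are set at 1, 6, 12 and 24 h.
- **Participant timeline {13}, Table 1:** 24 h and Discharge are separate columns, and QoR-40 is marked only under Discharge. The footnote describes "assessments — 24 h postoperatively".
- **Plans to promote participant retention {18b}:** "At the end of the hospital stay, as a standard 24 h after the surgery, study subjects will be encouraged to fill in the QoR-40".
- **Statistical methods for numerical outcomes with one-time measurement:** the list includes "QoR-40 score at discharge". The arms are compared by the Wilcoxon rank-sum test, with no reference to when the form was completed.
- **Objectives {7}:** the hypothesis is that "the investigated intervention would reduce opioid use and improve recovery with potentially fewer opioid side effects".

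**The concern.** Discharge happens after randomisation and may depend on how the patient is recovering. The article's own rationale makes this plausible: the Background says that opioid side effects (respiratory complications, sedation, nausea and vomiting) hold back early recovery, and the Objectives expect pregabalin to reduce opioid use and possibly those effects. A patient kept longer would be scored later, probably when feeling better. If the share kept longer differs by arm, the two sets of scores are not taken at a comparable time, and a rank-sum test that treats them as one measurement cannot tell better recovery from later measurement.

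At stake is a secondary outcome that bears on a stated hypothesis. NRS pain is also patient-reported, but QoR-40 is the only patient-reported measure of overall recovery. Among the postoperative outcomes listed, it alone has no fixed clock time. The primary outcome, 24 h oxycodone consumption, is not affected.

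**Working it through.** **1. Nominal time.** Four places (abstract, Outcomes, Table 1, analysis section) say discharge. Two (retention section, Table 1 footnote) point to 24 h. Read together, the intended time is about 24 h for most patients, but the defining event is discharge. The article states no rule for a patient still in hospital at 24 h. Table 1 and its footnote do not fit together for this row: if assessments are at 24 h, QoR-40 belongs in the 24 h column.

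**2. Form of the bias.** The plan has no figure to reproduce here: the article gives no QoR-40 SD, expected effect, daily gain, discharge criteria or length-of-stay data. Let pC and pT be the shares of control and pregabalin patients who stay an extra day, and g the mean gain in score over that day. Then

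measured difference = true difference at 24 h − g × (pC − pT).

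- If all leave at 24 h, pC = pT = 0 and the bias is nil.
- If the shares are equal, the bias in the mean is also nil.
- If pregabalin shortens stay (pC > pT), a true benefit shrinks.
- If pregabalin prolongs stay (pT > pC), its scores are raised by later measurement, and a true harm is partly hidden.

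**3. Illustration (all inputs assumed).** The true difference at 24 h is 0.5 SD in favour of pregabalin, scores are normal with SD 1, patients below a common recovery threshold stay one more day, and g is 0.25 to 1 SD. The pregabalin share follows from the control share: pT = Φ(Φ⁻¹(pC) − 0.5).

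| pC | pT | pC − pT | Measured difference, g = 0.25 to 1 SD | Share of 0.5 SD lost |
|---|---|---|---|---|
| 0 | 0 | 0 | 0.50 | 0 |
| 5% | 1.6% | 0.034 | 0.49 to 0.47 | 2 to 7% |
| 10% | 3.7% | 0.063 | 0.48 to 0.44 | 3 to 13% |
| 20% | 9.0% | 0.110 | 0.47 to 0.39 | 6 to 22% |
| 40% | 22.6% | 0.174 | 0.46 to 0.33 | 9 to 35% |

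For example, in the 10% row with g = 1: 0.5 − 1 × 0.063 = 0.437, and 0.063/0.5 = 13%. A simulation on the same assumptions agrees within its random error.

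**4. Effect on power.** Later scoring of the slowest patients also narrows the spread, so less power is lost than raw difference. With 45 per arm and a normal-theory comparison of means, power in the simulation is 66% with everyone scored at 24 h. It is 64 to 66% with 10% of controls late and 57 to 66% with 40% late. These figures only show scale; the planned test is the rank-sum test.

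**5. In score points.** If late stays differed by 10 to 30 percentage points and the gain were 5 to 10 points a day (both assumed), the loss would run from 0.10 × 5 = 0.5 to 0.30 × 10 = 3.0 points. The upper end needs at least 30% of controls to stay late, which fits poorly with 24 h as the standard. The article gives no SD or minimal important difference against which to judge these points.

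**The case against.** The case for leaving the plan alone is fair in several respects.

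- **Most patients should be scored at about 24 h anyway.** The retention section gives "At the end of the hospital stay, as a standard 24 h after the surgery", so bias can come only from those kept longer. This stands, and it limits the size.
- **Dependence of stay on recovery is an inference.** The article gives no discharge criteria, and stay could follow a fixed pathway or logistics. This also stands. The Background makes the link plausible but does not state it.
- **The direction is open.** The comparator section says that pregabalin's sedative effect is dose-related, and the Background notes a possible rise in adverse effects with remifentanil, so pregabalin could lengthen stay in some patients. This stands.
- **Other fixed-time evidence exists.** Ramsay, PONV impact and NRS pain are scored at fixed hours. This is true, but none of them measures overall recovery as the patient reports it.
- **Comfort at discharge is a definable outcome, and an article may leave windows and form details to the full protocol.** A missing window is indeed no finding. The point here rests on what the article does state: an event-based time, next to a table and footnote that do not match.

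A reader might infer that slower recoverers are in fact scored later here and that a real difference is therefore diluted. The documents do not support that: they give neither the share staying beyond 24 h nor any sign that it differs by arm.

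**Conclusion.** The point holds as a risk to one secondary outcome. QoR-40 is tied to an event that follows randomisation and may depend on treatment, with 24 h only as the usual time. If length of stay differs by arm, the comparison may be biased, probably towards no difference if pregabalin shortens stay and towards hiding a harm if it prolongs stay. The bias is nil if all leave at 24 h and probably small if few stay longer. The table above rests wholly on assumed values for the true difference, the daily gain and the share staying late. The change is worth making because it is cheap and removes the problem whichever way stay moves.

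**What to change.** Administer QoR-40 to every patient at the existing 24 h assessment, whether or not the patient is discharged then, and record the completion time on the form. Amend the abstract, Outcomes {12}, Table 1 (moving the mark to the 24 h column), the retention section {18b} and the one-time measurement section so that all say 24 h after surgery.

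For patients already enrolled, report a sensitivity analysis limited to forms completed at about 24 h, where a completion or discharge time is available. The article does not show that completion times have been recorded, so this may be possible for only some of them.

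Cost: no new visit or staff, since Table 1 already has a 24 h assessment. The change does need a protocol amendment, and under the amendments section {25} a significant modification goes to the Bioethics Committee and then to the registry. Patients enrolled before the change keep discharge timing, so the outcome will have mixed timing, and the report should say so.

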### Participant timeline {13}

The participant timeline is detailed in Table 1.

**Table 1 Tab1:** The participant timeline

	Study period							
	Enrollment	Allocation	Post-allocation					
Timepoint	− 1 day	Day of surgery	Surgery	1 h	6 h	12 h	24 h	Discharge
Enrollment:								
Eligibility screen	X							
Informed consent	X							
Allocation		X						
Interventions: pregabalin or placebo		X						
Assessment:								
Baseline variables	X	X						
Total oxycodone				- >	- >	- >	X	
The NRS scores				X	X	X	X	
Ramsay Score				X	X	X	X	
PONV-Impact score				X	X	X	X	
SatO2 < 94%				X	X	X	X	
Blurred vision				X	X	X	X	
Intraoperative SBP, DBP, MBP and HR			X					
Total fluid			X					
Total ephedrine			X					
QoR-40								X

Enrolment — 1 day before the operation, intervention — 1 to 2 h before surgery, assessments — 24 h postoperatively

### Sample size {14}

The primary outcome of the study is 24-h oxycodone consumption. The mean 24-h oxycodone consumption in our previous study was 31.31 mg in patients on multimodal anesthesia [18] and SD was 13.7. In order to calculate sample size, we made the following assumptions: type 1 error (*α*) was set at 0.05; type 2 error (*β*) at 0.9 based on two-tailed testing. We considered a difference between groups (*δ*) greater than 10 mg, this being roughly 30% of the mean dose given above, and a standard maximal single dose of oxycodone in an adult patient, to be clinically significant. Using a sample size formula for two-tailed testing recommended in [27], a sample size of 76 should be enough to detect a substantial difference, as stated above. Taking into account an assumed mean drop-out of 15%, we have adopted a rounded-up sample size of 90 patients.

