## Discussion

We describe the protocol of a clinical trial to evaluate the effect of preemptive oral pregabalin administration as an element of multimodal analgesia strategy in patients undergoing LSG, which is most commonly performed in bariatric surgery [41]. Given the limited number of clinical trials and methodological restrictions in existing publications [8–11], which demonstrate varying but significant opioid use reduction in the postoperative period as well as the scarce amount or absence of studies focusing on other significant aspects, additional evidence is required before incorporating pregabalin into a multimodal regimen in the perioperative management of LSG [42].

Our study’s possible limitation may be the use of a *z*-test for the primary outcome to estimate the sample size, while we expect the use of a non-parametric test in the analysis. Therefore, the non-parametric analysis may not reach 90% power. However, as we applied a 15% larger sample size, it may compensate for using a non-parametric test.

In conclusion, the results of the trial based on our protocol will aim at filling this gap and provide us with evidence on the effect of pregabalin administration in a dose of 150 mg on opioid consumption, pain scores, quality of recovery, and hemodynamic stability, which may contribute to a reassessment of recommendations to use this drug in the patients undergoing LSG.

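### The stated inputs need 80 evaluable patients, not 76, and the 15% offered as cover for the rank test is already assigned to drop-out

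*Protocol article*

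**What the plan says.** The section Sample size {14} of the protocol article takes a mean of 31.31 mg and an SD of 13.7 from the group's previous study, and treats a difference above 10 mg as clinically significant. It states "type 1 error (*α*) was set at 0.05" and "type 2 error (*β*) at 0.9 based on two-tailed testing". From these it concludes that "a sample size of 76 should be enough to detect a substantial difference, as stated above". It then adds: "Taking into account an assumed mean drop-out of 15%, we have adopted a rounded-up sample size of 90 patients".

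The section on numerical outcomes with one measurement fixes the Wilcoxon rank sum test for the primary outcome, on the assumption that the data are not normal.

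The Discussion explains that a z-test was used for sizing although a non-parametric analysis is expected, and concedes that "the non-parametric analysis may not reach 90% power". The next sentence reads: "However, as we applied a 15% larger sample size, it may compensate for using a non-parametric test".

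**The concern.** Three statements about the primary endpoint do not fit together.

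- The figure of 76 does not follow from the inputs printed beside it.
- A type 2 error of 0.9 means, literally, 10% power.
- The allowance that the sample size section sets aside for drop-out appears again in the Discussion as a reserve for the rank test. No second increase is described anywhere.

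What is at stake is how a reader judges a non-significant result. The article presents 76 as sufficient for the target, and the sentence that follows its own warning about the rank test weakens that warning. Someone who checks the calculation will not recover 76 and will not know which input to distrust.

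**Working it through.** **Inputs.** From Sample size {14}: SD 13.7 mg, difference 10 mg, alpha 0.05 two-sided, 76 evaluable, 15% drop-out, 90 enrolled. From Trial design {8}: 1:1 allocation. From the Discussion: z-test for sizing, 90% power. The last item shows that the printed 0.9 is the power, so the type 2 error is 0.1.

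**Attempt to reproduce 76.** n per arm = 2 x (1.960 + 1.282)² x 13.7² / 10² = 39.44. Rounded up, this is 40 per arm and 80 in total; unrounded, the total is 78.9. Rounding therefore does not explain 76. Other readings, as totals:

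| Variant | Total |
|---|---|
| 80% power | 60 |
| 85% power | 68 |
| One-sided, 90% power | 66 |
| t-test, 90% power | 82 |
| Difference = 30% of 31.31 (9.39 mg) | 90 |
| Difference = one third of 31.31 (10.44 mg) | 74 |
| Difference = 10.2 or 10.3 mg | 76 |

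Only a difference of about 10.2 to 10.3 mg, or equivalently an SD of about 13.45, returns 76. Neither is stated.

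**Power at 76 (38 per arm).** 10 / (13.7 x √(2/38)) − 1.960 = 3.182 − 1.960 = 1.222, which gives 88.9% for the z-test. The noncentral t distribution gives 88.1% for the t-test.

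**Drop-out step.** 76 / 0.85 = 89.4, rounded up to 90; this step reproduces. In reverse, 90 x 0.85 = 76.5, so the assumed drop-out uses the whole increase. Starting from 80, the same step gives 80 / 0.85 = 94.1.

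**Wilcoxon power, difference 10 mg, SD 13.7.** The documents do not give the shape of the distribution, so these rows rest on assumptions. Under normality, the lower figure is from simulation (20,000 runs) and the higher from the asymptotic efficiency 3/π = 0.955 applied to the z formula. The gamma row is simulated with means 31.31 and 21.31 and SD 13.7 in both arms. The last row uses 0.864, the lowest asymptotic efficiency for a pure shift.

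| Assumed shape | 76 evaluable | 80 evaluable | 90 evaluable |
|---|---|---|---|
| Normal | 86.3–87.5% | 87.9–89.1% | 91.7–92.3% |
| Gamma (skewed) | 92.9% | 94.1% | 96.5% |
| Lowest efficiency | 84.1% | 85.9% | 89.6% |

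**How much drop-out the reserve can bear.** Under normality the Wilcoxon test needs about 42 to 43 per arm for 90% power, that is 84 to 86 evaluable. From 90 enrolled this allows 4 to 6 losses: 4/90 = 4.4% and 6/90 = 6.7%, against the assumed 15%.

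**The case against.** A reader might infer that the trial does not have 90% power for its primary endpoint, or is seriously underpowered. The documents do not support that, for four reasons.

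- **Shape.** The figure of 86–87% needs normal data, whereas the article chooses the Wilcoxon test because it expects non-normal data. Under the gamma shape the planned test exceeds 90% even after full drop-out. That shape is an assumption too, so neither figure can be called the power of the trial.
- **Disclosure.** The Discussion itself warns that the non-parametric analysis may miss 90%. Nowhere does the article claim 90% for the Wilcoxon test.
- **Losses.** The section on missing data expects very few missing primary values, because consumption comes from an electronic pump log. The section on discontinuation calls disqualification after randomization rare. The compensation sentence says only that the larger sample may help, and with few losses it does.
- **Size.** The z-test falls about one point short at 76. The text speaks of a difference greater than 10 mg, and the cited source of the formula is not at hand.

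All of this limits the consequence. It does not make 76 right at 10 mg, and it does not free the 15% for a second use under the drop-out that the sample size section itself assumes. The misprinted type 2 error is unlikely to mislead anyone who reads the Discussion, but it stands in the paragraph that defines the design.

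**Conclusion.** The concern holds as a minor correction of stated figures. At a difference of 10 mg and an SD of 13.7, the z formula requires 80 evaluable patients. The stated 76 is 4 short and gives 88.9% power instead of 90%. The type 2 error is misprinted.

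The compensation argument is conditional: the allowance covers the rank test only if losses stay well below 15%. With normal data and full drop-out together, Wilcoxon power is about 2.5 to 4 points under target. With little drop-out, or with data skewed as in the gamma case, the gap closes or reverses. The z and t figures rest only on the article's inputs; the Wilcoxon figures also depend on the assumed distribution.

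**What to change.** Keep 90 patients and make three changes of wording.

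1. In Sample size {14}, give the type 2 error as 0.1 (90% power).
2. In the same section, state either that the z formula needs 80 evaluable patients, or that 76 gives about 89% power. If a difference other than 10 mg was entered, print it. If 80 is stated, add that 90 enrolled with 15% drop-out leaves about 76.
3. In the Discussion, keep the warning about the rank test and replace the compensation sentence with Wilcoxon power as a range: under normality about 86–87% with 76 evaluable and about 92% with all 90; higher if the data are skewed, for example about 93% at 76 under an assumed gamma shape with the same means and SD.

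There is no change to the number of patients, the test or the endpoint. The only cost is that the stated power becomes slightly less favourable and openly conditional.

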### Recruitment {15}

Patient recruitment starts in April 2023 and is planned to end before April 2025. There will be 4 dedicated investigators responsible for the screening and recruitment of potential participants. All patients qualified for the primary laparoscopic sleeve gastrectomy are identified, screened, and approached if they meet inclusion and do not have exclusion criteria. All patients, prior to study inclusion and signing the consent forms, are reassured that their participation in this trial is entirely voluntary and that refusing to participate or withdrawal at any time during the study would not result in any kind of penalty or negative consequences for the patient.

